## Methods: participants, interventions, and outcomes

### Study setting {9}

This study is a multicenter trial conducted at 10 hospitals in South Korea to generalize the results, and 10 hospitals are located in various cities.

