## Eligibility criteria {10}

### Inclusion criteria

18 years old or olderPatients who have been confirmed of COVID-19 infection and has evidence for pneumonia
A.Confirmation of COVID-19 infection by RT-PCR of SARS-CoV-2B.Definite diagnosis of new infiltration of the lungs by chest CT scan of chest radiographic inspection3.Patients who are within 72 h of COVID-19 pneumonia confirmation4.Patients with 3 (hospitalization, not requiring supplemental oxygen) or higher in seven-category ordinal scale of clinical status5.Patients who are eligible for diagnosis/evaluation to chest CT scan and related to it6.Patients should be able to understand the essence of the clinical trial and to submit a written consent document. For the patients who can understand the nature of the research but cannot sign the document, a relative can agree to the study.

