## Outcomes {12}

### Primary outcome

The primary outcome is as follows: proportion of patients with clinical improvement as defined by live discharge from hospital or a decline of 2 categories on the seven-category ordinal scale of clinical status [time frame: day 14 and day 28]

*Seven-category ordinal scale of clinical status
Not hospitalized with resumption of normal activities;Not hospitalized, but unable to resume normal activities;Hospitalization, not requiring supplemental oxygen;Hospitalization, requiring supplemental oxygen;Hospitalization, requiring nasal high-flow oxygen therapy and/or noninvasive mechanical ventilation;Hospitalization, requiring extracorporeal membrane oxygenation and/or invasive mechanical ventilation;Death.

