**ASSESSMENTS:**									
*[SARS-CoV RT-PCR]*	X			X	X	X	X		
*[Chest X-ray]*	X			X	X	X	X		
*[Chest CT]*	X						X		
*[Physical examination]*	X								
*[Viral signs]*	X		X	X	X	X	X	X	X
*[Symptoms]*	X		X	X	X	X	X	X	X
*[Seven category ordinary scale]*	X		X	X	X	X	X	X	X
*[NEWS score]*	X				X		X	X	X
*[Blood test]*	X		X	X	X	X	X	X	X
*[Blood collection for research]*			X		X				
*[Adverse reaction]*			X	X	X	X	X	X	X

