### Sample size {14}

The sample size was calculated based on the assumption that superiority test (nafamostat treatment is right) of the treatment effect (effect size 10%) between two treatment groups (control group vs. nafamostat-treated group) will be carried out. The superiority margin is set to 0.05 (5%) based on the assumption that the nafamostat-treated group shows higher effect (90.0%) over the control group (80.0%). Nafamostat will be concluded as effective when the nafamostat-treated group shows 5% of higher effect compared to the treatment rate of the control group (80%). A one-sided significance level of 0.05 and power of 80% with equal allocation to two arms would require 42 patients in each arm of the trial.

Basic parameters for the sample size calculation are as follows:
Significance level, alpha = 0.05 (one-sided test)Power = 70%/80%/90%The ratio of the control group and the experimental group (nafamostat treatment) patients is 1:1Cure rate of the control group: 80%The cure rate of the experimental group (nafamostat treatment): 90%Superiority margin: 5%Expected drop out proportion: 5% (control, experimental each)

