## Assignment of interventions: allocation

### Sequence generation {16a}

Nafamostat mesylate with standard therapy group and standard therapy only group were assigned in a 1:1 ratio by block randomization method by institution.

The randomization generation program is as follow: randomization codes are generated using SAS® (SAS Institute, Cary, NC, USA) and assigned to a test group (nafamostat administration + standard treatment) or a control group (standard treatment) according to the generated assignment order.

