## Data collection and management

### Plans for assessment and collection of outcomes {18a}

Data on demographic information, underlying disease, initial symptoms, diagnosis date, coronavirus Ct value, and laboratory and radiological findings is collected by the clinician. The clinician evaluates the seven-category ordinal scale of clinical status on admission, NEWS score and clinical course complications at hospitalization, treatment progress and clinical results, and side effects by drugs. Medical history is collected within 1 year before screening. In the case of single malignant tumors, medical history within 5 years before screening is collected. Information about underlying disease such as diabetes, hypertension, liver cirrhosis, chronic kidney disease without hemodialysis, end-stage renal disease, chronic heart failure, and lung diseases is collected regardless of period. At each visit, the National Cancer Institute Adverse Events Standard Terminology (NCI CTCAE) version 5.0 should be documented and recorded. The collection period for these reactions is from the start of treatment in the test or control group to day 28.

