## Statistical methods

### Statistical methods for primary and secondary outcomes {20a}

Intention-to-treat analysis and per protocol analysis will be conducted respectively, and intention-to-treat analysis will be performed as the main analysis.The categorical variable of the evaluation index will be analyzed using Pearson’s chi-square test, and the continuous variable will be analyzed using ANOVA or Kruskal–Wallis test.The virus removal rate on day 14, one of the secondary outcomes, will be analyzed using Pearson’s chi-square test.Time to clinical improvement will be assessed on all subjects by day 28. If there is no clinical improvement or a case of death by day 28, it will be recorded as day 28, and analyzed by Kaplan–Meier plot and log-rank test.

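### The primary comparison is not adjusted for baseline ordinal category, which sets each patient's success hurdle; the test stays valid, but precision is given up and chance severity imbalance is left uncorrected

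*Protocol article*

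**What the plan says.** All references are to the protocol article.

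- **Test.** Statistical methods {20a}: "The categorical variable of the evaluation index will be analyzed using Pearson’s chi-square test". The primary outcome is a categorical (yes/no) variable, so this is its test, with intention to treat as the main analysis. Time to clinical improvement gets a Kaplan-Meier plot and a log-rank test. Neither has a covariate or stratum. The section on additional analyses {20b} adds none.
- **Outcome.** Primary outcome {12}: "proportion of patients with clinical improvement as defined by live discharge from hospital or a decline of 2 categories on the seven-category ordinal scale", at day 14 and day 28.
- **Entry range.** Inclusion criteria {10}: "Patients with 3 (hospitalization, not requiring supplemental oxygen) or higher in seven-category ordinal scale of clinical status". Living inpatients therefore enter in categories 3 to 6.
- **Randomization.** Sequence generation {16a}: the groups "were assigned in a 1:1 ratio by block randomization method by institution". Severity is not a stratum.
- **Baseline value.** The participant timeline {13} marks the "Seven category ordinary scale" at screening, and section {18a} says that "The clinician evaluates the seven-category ordinal scale of clinical status on admission".

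**The concern.** Success is measured from the patient's own starting category, so the hurdle differs by entry group. From category 3 or 4, a two-category decline means leaving hospital. From category 5, reaching category 3 (in hospital, no oxygen) is enough; from category 6, reaching category 4 (in hospital, on oxygen) is enough. The chi-square test pools these groups.

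With 42 patients per arm and blocking by institution only, the share of sicker patients in each arm is left to chance. If success rates differ between entry groups, an imbalance moves the raw risk difference, and the planned analysis cannot correct it even though the covariate is on file. The trial is open label, so an adjustment introduced after an imbalance has been seen would look post hoc. That is a reason to settle it in advance.

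**Working it through.** **The plan's own figure.** Sample size {14}: "A one-sided significance level of 0.05 and power of 80% with equal allocation to two arms would require 42 patients in each arm", from 80% against 90%, a 5-point margin and 5% dropout. The usual formula gives (1.645 + 0.842)² × (0.16 + 0.09) / (0.10 − 0.05)² = 619 per arm before dropout; without the margin the divisor is 0.10² and n = 155. The 42 is not reproduced. At 42 per arm, power is about 36% without the margin and about 16% with it. That is a separate problem; here it only shows that precision is scarce.

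**Inputs for the imbalance check.** From the documents: n = 42 per arm, 80% control success, one-sided 0.05. Not in the documents, so assumed: q, the share of patients in categories 5-6, and D, the gap in success rate between categories 3-4 and 5-6. The range used is q = 0.15 to 0.30 and D = 27 to 40 points, with overall success held at 80%. For q = 0.30, D = 40 means 92% against 52%, and D = 27 means about 88% against 61%.

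**Formulas.**
- SD of the between-arm difference in severe share: √(2q(1−q)/42). For q = 0.15 this is 7.8 points; for q = 0.30, 10.0 points.
- Shift in the raw risk difference (no drug effect): D × imbalance. Mean absolute shift is about 0.80 × D × SD.
- Share of outcome variance explained by the two strata: q(1−q)D²/(0.8 × 0.2).

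| q, D | Mean absolute shift | Trials with shift of 5 points or more | Variance explained |
|---|---|---|---|
| 0.15, 27 points | 0.80 × 0.27 × 7.8 = 1.7 points | 2% | 0.1275 × 0.0729 / 0.16 = 6% |
| 0.30, 27 points | 0.80 × 0.27 × 10.0 = 2.2 points | 7% | 0.21 × 0.0729 / 0.16 = 10% |
| 0.30, 40 points | 0.80 × 0.40 × 10.0 = 3.2 points | 19% | 0.21 × 0.16 / 0.16 = 21% |

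The third column uses exact binomial counts in each arm. With D = 10 points, even a 1.96-SD imbalance shifts the result by only about 2 points.

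**Given an imbalance.** With q = 0.30, the severe share differs by at least 10 points in 28% of trials, counting both directions (14% each way). In those trials the raw difference is off by about 3 to 6 points over the assumed range, while the Mantel-Haenszel estimate is within about 0.2 points of the truth.

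**Error rates (simulation, simple 1:1 allocation).** Over all randomizations, the unadjusted one-sided test rejects a true null in 5.0 to 5.2% of trials. Given an imbalance of at least 10 points that favours nafamostat, with q = 0.30, it rejects in about 12% (D = 27) to 16% (D = 40), against about 5% for the stratified test.

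**Power (zero difference tested, no margin).** For 80% against 90%: from about 36% to 37% (q = 0.20, D = 30) and to 39% (q = 0.30, D = 36). With q = 0.30, D = 40 and an odds ratio of 2.25 (success 88.7%, slightly under plan): from 30% to 33%. At the upper edge, with the effect set at exactly 10 points, the gain is about 4 points; at q = 0.40, D = 40, outside the range above, it is about 5.

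**The case against.** The strongest reply is that nothing here is an error. An unadjusted chi-square test is valid in a randomized trial, and chance imbalance is already part of its 5% error rate. **This stands.** The case for adjustment rests on precision and on behaviour given the imbalance actually seen.

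Second, an article condenses the protocol, and adjustment is often left to the analysis plan. This weakens the point without removing it, because the article names the test for the primary outcome.

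Third, the size rests on inputs that the documents do not give. **This stands too.** Consent requires a patient who can understand the trial, and those at high risk of death within 3 days are excluded; both may limit category 6. Patients in categories 5-6 can also succeed while still in hospital, which narrows the gap and leaves even its direction unstated. Blocking by institution would reduce imbalance if severity clusters by hospital, and the simulations ignore this.

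A reader might infer that imbalance will typically move the result by about half the planned effect, 5 of 10 points. The documents do not support that. Such a shift needs a large assumed gap together with a selected minority of trials; the average over all trials is 2 to 3 points.

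Finally, two strata still pool categories 5 and 6, whose hurdles differ, and leave out institution. With 84 patients at 10 hospitals, finer strata would be sparse, so pooling in advance is a reasonable compromise.

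**Conclusion.** The point holds as an improvement to a stated method that needs no new data. It does not show that the planned test is invalid or systematically biased. From the documents alone: the named tests are unadjusted, entry category sets the success hurdle, it is recorded before treatment, and randomization does not balance it.

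The size is conditional on q = 15 to 30% and D = 27 to 40 points. On those assumptions, stratifying removes an average absolute shift of about 2 to 3 points, restores the error rate in trials with marked imbalance, and reduces variance by about 6 to 21%. The power gain is about 1 to 3 points over most of the range and slightly more at its upper edge. If the prognostic gap is small, all of these gains are small. The change would not rescue a comparison with about 36% power, because 42 per arm does not follow from its own inputs.

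**What to change.** Before outcome data are examined, specify:

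1. **Primary analysis:** a Cochran-Mantel-Haenszel test with the Mantel-Haenszel risk difference and its confidence interval, stratified by the baseline ordinal category recorded at screening (3-4 against 5-6), with a rule fixed in advance for pooling sparse categories. A standardised risk difference from a logistic model containing baseline category is an acceptable alternative.
2. **Time to clinical improvement:** a log-rank test stratified by the same two groups.
3. **Sensitivity analysis:** the unadjusted Pearson chi-square comparison.

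The cost is a change of analysis wording. The baseline value is already scheduled, and no visit, treatment or randomization procedure changes. The sample size justification needs its own correction.

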### Secondary outcome

#### Clinical outcome

Time to clinical improvement (TTCI) [time frame: up to 28 days]
A.Time to clinical improvement (TTCI) was defined as time from randomization to a decline of 2 categories on the seven-category ordinal scale of clinical status or live discharge from the hospital, whichever came firstClinical status assessed by 7-category ordinal scale on days 7, 14, and 28Change in National Early Warning Score (NEWS) from baseline to day 28 [time frame: day 1 through day 28]*The NEW score has demonstrated an ability to discriminate patients at risk of poor outcomes. This score is based on 7 clinical parameters (respiration rate, oxygen saturation, any supplemental oxygen, temperature, systolic blood pressure, heart rate, level of consciousness). The NEW Score is being used as an efficacy measureTime to National Early Warning Score (NEWS) of ≤ 2 and maintained for 24h 28 [time frame: day 1 through day 28]Duration of hospitalization [time frame: day 1 through day 28] measured in daysDuration of new non-invasive ventilation or high flow oxygen use [time frame: day 1 through day 28]Incidence of new non-invasive ventilation or high flow oxygen use [time frame: day 1 through day 28]Duration of new supplement oxygen use [time frame: day 1 through day 28]Incidence of new supplement oxygen use [time frame: day 1 through day 28]Duration of new ventilator or extracorporeal membrane oxygenation (ECMO) use [time frame: day 1 through day 28]Incidence of new ventilator or extracorporeal membrane oxygenation (ECMO) use [time frame: day 1 through day 28]Mortality at day 28 [time frame: day 1 through day 28]. Date and cause of death (if applicable)Time (days) from treatment initiation to death

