## Methods in analysis to handle protocol non-adherence and any statistical methods to handle missing data {20c}

Outcome data obtained from all randomized participants will be included in the main analyses to prevent attrition bias. To prevent missing data, the researcher, trained research nurse, and research assist will double check the data as well as the recording of reasons for missing data. By replacing missing data with the mean or median value, we plan to analyze with minimal data loss.

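### Kaplan–Meier and log-rank are named only for time to clinical improvement; the only stated rule left for time to NEWS ≤ 2 and time to death is ANOVA or Kruskal–Wallis, with no rule for patients without the event

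*Protocol article*

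**What the plan says.** Section {20a} of the protocol article covers primary and secondary outcomes and sets two general rules. For categories: "The categorical variable of the evaluation index will be analyzed using Pearson’s chi-square test". For everything measured on a continuous scale: "the continuous variable will be analyzed using ANOVA or Kruskal–Wallis test".

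One event time is then treated separately: "Time to clinical improvement will be assessed on all subjects by day 28". Patients without that event are given a value ("If there is no clinical improvement or a case of death by day 28, it will be recorded as day 28"), and the method is Kaplan–Meier with log-rank.

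The secondary clinical outcomes list two further event times. One is the time until NEWS is 2 or lower and stays there for 24 hours. The other is "Time (days) from treatment initiation to death". Section {20a} mentions neither. Day-28 mortality is listed as a separate secondary outcome.

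Section {20c} keeps all randomized participants in the main analyses and adds: "By replacing missing data with the mean or median value, we plan to analyze with minimal data loss".

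**The concern.** A survivor has no time to death, and a patient who never reaches NEWS ≤ 2 has no time to it. ANOVA and Kruskal–Wallis need a number for every patient analysed. The analyst must therefore drop these patients, fill in a value, or score them at the end of follow-up.

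Dropping them compares timing within a subset selected by the outcome, so the comparison is no longer a randomized one. Filling with the mean or median gives a survivor a typical time of death, and gives a patient who never recovered a typical recovery time. In both cases a treatment that changes how many patients have the event, but not when, leaves almost no trace in the test.

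Rapid recovery from symptoms is part of the main hypothesis in Objectives {7}, and NEWS recovery has no companion endpoint that counts how many patients reach it.

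**Working it through.** **1. Which stated rule covers which event time**

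| Event time | Method named in {20a} | Value for non-events in {20a} | Companion proportion endpoint |
|---|---|---|---|
| Clinical improvement | Kaplan–Meier, log-rank | day 28 | yes (primary outcome) |
| NEWS ≤ 2 for 24 h | none; only the continuous rule fits | none | no |
| Death | none; only the continuous rule fits | none | yes (day-28 mortality, chi-square) |

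The plan states no power or event rate for these endpoints, so there is no figure of its own to reproduce.

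**2. Inputs for the size of the problem**

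From the plan: 42 per arm and follow-up to day 28. Assumed: the event rates, the hazard ratios (HR), whole-day event times and two-sided 5% tests. With exponential times, a control 28-day probability p gives a treated probability of 1 − (1 − p)^HR:

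- NEWS, HR 2: p = 0.50, 0.70, 0.80, 0.90 gives 0.75, 0.91, 0.96, 0.99.
- Death, HR 0.25, p = 0.20: 1 − 0.80^0.25 = 0.054. Expected deaths are 42 × 0.20 = 8.4 and 42 × 0.054 = 2.3, so a test among deaths has about 11 patients.

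**3. Time to NEWS ≤ 2, HR 2: power by scoring of non-events** (1,500 replicates; standard error about 1 point)

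| Controls reaching it | Log-rank, all patients | KW, observed times only | KW, median-filled | KW, mean-filled |
|---|---|---|---|---|
| 50% | 72% | 13% | 10% | 14% |
| 70% | 80% | 22% | 21% | 30% |
| 80% | 83% | 36% | 35% | 44% |
| 90% | 88% | 56% | 55% | 63% |

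(KW = Kruskal–Wallis.) The loss shrinks as more patients reach the event, because fewer times are absent. A separate run of the same design gave log-rank 71–85%, observed times only 13–55% and median-filled 11–55%.

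With non-events scored at day 28 (another run, 2,000 replicates):

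| Controls reaching it | Log-rank | KW, day-28 score | Loss |
|---|---|---|---|
| 50% | 71% | 67% | 4 |
| 70% | 83% | 74% | 9 |
| 80% | 85% | 78% | 7 |
| 90% | 88% | 77% | 11 |

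The separate run gave 68–76% with the day-28 score; at the low end the loss is 71 − 68 = 3 points.

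**4. Time to death, 20% control mortality, HR 0.25**

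Log-rank 56%; KW 3% on deaths only, 1% median-filled and 3% mean-filled. With survivors scored at day 28, KW has 53% against 54% for log-rank in the same run.

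**5. Only the share with the event differs; timing is identical** (assumed gamma times, mean about 10 days; 2,000 replicates)

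| Event share, control vs nafamostat | KW observed only | KW median-filled | KW day-28 | Log-rank | Chi-square |
|---|---|---|---|---|---|
| Recover 50% vs 80% | 5% | 5% | 70% | 80% | 85% |
| Recover 60% vs 90% | 5% | 5% | 67% | 84% | 91% |
| Recover 80% vs 90% | 5% | 5% | 12% | 20% | 26% |
| Die 20% vs 5% | 3% | 1% | 58% | 59% | 60% |
| Die 30% vs 5% | 3% | 0.4% | 90% | 90% | 91% |

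With observed-only or median-filled times, the test rejects at or below its nominal 5% however far apart the shares are. For deaths, chi-square on day-28 mortality does as well as log-rank.

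**The case against.** Several counter-arguments have weight.

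- **The assignment is inferred.** Section {20a} names neither endpoint under the continuous rule, and the one event time it does name is not treated as a continuous variable. Being singled out is not proof of exclusivity either: viral clearance on day 14 gets its own chi-square sentence although the categorical rule already covers it. The article condenses a full protocol, and an analysis plan could assign log-rank. This stands as a limit on the claim. It does not remove the point, because the article fixes a general rule for primary and secondary outcomes and exempts one event time by name. Followed as written, it leaves the other two under an unsuitable test.
- **A reader might infer that the plan compares only patients who had the event.** The documents do not say so. Intention-to-treat is the main analysis and {20c} includes all randomized participants. But including everyone requires a value for each non-event, and the general replacement rule in {20c} is mean or median, which performs little better. Whether a survivor's absent death time counts as missing data under {20c} is itself unclear. The harmless choice, day 28, is written for time to clinical improvement only.
- **A reader might infer that the trial would miss prevented deaths.** It would not: day-28 mortality is tested separately. The blindness belongs to the time-to-death test alone. More frequent or earlier improvement is likewise tested by the primary outcome and by time to clinical improvement.
- **The assumed effects are large.** At 80% against 90%, the rates used in the sample size section for the primary outcome, log-rank itself has only 20% power. The participant timeline schedules NEWS at screening and days 7, 14, 21 and 28, whereas the simulations use daily times. The figures show the order of the loss, not a forecast.

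**Conclusion.** The point holds as a defect in how the analysis rule is written. For time to NEWS ≤ 2 and time to death, the only stated rule that fits is one that does not handle censoring, and no value is set for patients without the event.

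The size depends on a choice the article leaves open. Under assumed rates with 42 per arm and HR 2, observed-only or median-filled Kruskal–Wallis has about 11–55% power against 71–85% for log-rank; mean-filling gives 14–63%. Day-28 scoring would lose only about 3–11 points in that setting, and at most 84 − 67 = 17 points where only the share recovering differs.

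The practical consequence falls mainly on NEWS recovery. These are secondary endpoints and the primary analysis is unaffected, but the change is worth making.

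**What to change.** In section {20a}, extend the Kaplan–Meier and log-rank sentence to time to NEWS ≤ 2 sustained for 24 hours and to time to death, on all randomized patients.

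- **NEWS:** record patients who die or do not reach the threshold as not reached, censored at day 28, in line with the rule for time to clinical improvement.
- **Death:** censor survivors at day 28 or when last known alive.
- **Replacement:** state in {20c} that mean or median replacement does not apply to event times, and in {20a} that ANOVA or Kruskal–Wallis does not either.

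The cost is a few lines of text. It needs no new data, patients or procedures, and the method is already planned for time to clinical improvement.

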## Objectives {7}

### Research hypothesis

The main hypothesis of this study is that it shows a rapid recovery from symptoms and viral suppression in the intervention group.

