### Secondary objective

Secondary objective comprised change in National Early Warning Score, duration of hospitalization, incidence of new-non-invasive ventilation or high flow oxygen use or ventilator, mortality at day 28, viral load change, and adverse events.

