#### Virological endpoints

1. Proportions of patients with a negative nasopharyngeal swab and sputum sample for SARS-CoV-2 quantitative RT-PCR on days 3, 7, 10, 14, and 21 after starting treatment

2. Viral load change (log10 viral load) of nasopharyngeal swab and sputum sample for SARS-CoV-2 quantitative RT-PCR on days 3, 7, 10, 14, and 21 after starting treatment

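### Viral load is measured serially in two specimens, but the only method stated for continuous outcomes is a cross-sectional ANOVA or Kruskal–Wallis test, and no key viral-load comparison is named

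*Protocol article*

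**What the plan says.** - **Method.** Statistical methods for primary and secondary outcomes {20a} has a single rule for continuous outcomes: "the continuous variable will be analyzed using ANOVA or" Kruskal–Wallis. The section is more specific elsewhere. It ties the virus removal rate to day 14 with a chi-square test, and gives a day-28 recording rule, a Kaplan–Meier plot and a log-rank test for time to clinical improvement. For viral-load change it names no day, specimen or contrast.
- **Endpoint.** Virological endpoints lists "Viral load change (log10 viral load) of nasopharyngeal swab and sputum sample", assessed "on days 3, 7, 10, 14, and 21 after starting treatment".
- **Schedule.** In the Participant timeline table, the row "SARS-CoV RT-PCR" is marked at screening and on days 3, 7, 10 and 14. Day 21 is not marked.
- **Missing data.** Section {20c} plans to replace missing values with the mean or median.
- **Standing of the outcome.** The Research hypothesis speaks of "rapid recovery from symptoms and viral suppression in the intervention group". The Secondary objective lists "mortality at day 28, viral load change, and adverse events".

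**The concern.** The stated method does not fit how the outcome is measured. A Kruskal–Wallis test compares independent groups and cannot use repeated measurements within a patient. ANOVA is offered as its parametric counterpart, so a one-way ANOVA between arms is the natural reading. Applied to serial data, each test uses one day and one specimen and discards what the same patient's other samples show.

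Three things follow. Precision is lost in a trial with only 42 patients per arm. A patient who lacks a later sample receives a filled-in value although earlier samples exist. And there are several viral-load comparisons, none marked in advance as the one to be read as the result for that outcome. The last point has some weight because the Research hypothesis mentions viral suppression.

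**Working it through.** **The plan's own figure.** The article gives no sample size, power or error rate for viral load, so there is none to reproduce. The 42 per arm was set for the binary primary outcome and is used here only as the number available.

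**Number of comparisons, if tested by day and specimen.**
- Endpoint list: 5 days × 2 specimens = 10.
- Schedule table: 4 days × 2 specimens = 8.

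**Precision of an average over days.** The documents give no correlations. I assume equal correlation ρ between days and an equal effect on every day. The variance of a k-day mean relative to one day is (1 + (k − 1)ρ)/k.

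| ρ | 4 days | 5 days |
|---|---|---|
| 0.3 | 0.475 | 0.44 |
| 0.5 | 0.625 | 0.60 |
| 0.7 | 0.775 | 0.76 |
| 0.8 | 0.85 | 0.84 |

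An ANOVA F test and a Kruskal–Wallis test are non-directional, so two-sided 0.05 is the matching level. The one-day effect detectable with 80% power is (1.960 + 0.842) × √(2/42) = 2.802 × 0.218 = 0.61 SD. For the five-day average it is 0.61 × √0.44 = 0.41 SD to 0.61 × √0.84 = 0.56 SD. An effect with 80% power on one day would have 86% to 99% power on the five-day average.

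**How far this depends on a persistent effect.** Take an assumed effect of 0.375 SD and the four scheduled days. For one day, z = 0.375/0.218 = 1.72. For the average, z = 1.72 × (days affected/4)/√((1 + 3ρ)/4).

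| Comparison | Power, two-sided 0.05 | Power, one-sided 0.05 |
|---|---|---|
| One affected day | 40% | 53% |
| Average, all 4 days affected, ρ = 0.3 / 0.5 / 0.7 | 70 / 58 / 50% | 80 / 70 / 62% |
| Average, 3 of 4 days affected, ρ = 0.5 | 37% | 49% |
| Average, 2 of 4 days affected, ρ = 0.5 | 19% | 29% |

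The average is better than one affected day only when (days affected)/4 exceeds √((1 + 3ρ)/4). At ρ = 0.5 that threshold is 0.79, so three days of four (0.75) are not enough. At ρ = 0.3 it is 0.69, and three days are enough.

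**Baseline adjustment.** The endpoint is a change, and the schedule has a screening RT-PCR. With baseline-to-follow-up correlation r and equal variances, a raw change has variance 2(1 − r), and the baseline-adjusted value has 1 − r². The ratio is (1 + r)/2, or 0.65 to 0.90 for r from 0.3 to 0.8. This gain holds for a single-day contrast too and needs no persistent effect.

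**False positives, if each test were read alone at 0.05.** If the tests were independent, the chance of at least one would be 1 − 0.95^8 = 0.34 or 1 − 0.95^10 = 0.40. They are not independent. In simulations of two-sided tests with 42 per arm, between-day correlation 0.3 to 0.8 and between-specimen correlation 0.5 to 0.9 (all assumed), the chance is about 0.16 to 0.30 for eight tests and 0.17 to 0.37 for ten.

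**Effect of filling in values.** As an illustration, apply the 5% dropout of the sample-size section: 0.05 × 42 is about 2 patients per arm. Suppose they are filled with their own arm's mean (the article does not say which mean). The sum of squares is unchanged but is divided by 41 instead of 39, and n counts as 42 instead of 40. The apparent standard error is √((39/41) × (40/42)) = 0.95 of the honest one. The understatement grows with the share of missing samples.

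**The case against.** The strongest reply is that this is mostly silence about a secondary outcome. The sentence in {20a} is generic. It does not speak of separate tests by day, and it does not exclude a repeated-measures ANOVA or a summary measure. A key day, a key specimen, a multiplicity rule and the model are commonly left to an analysis plan, which is not shown here, and the article condenses a fuller protocol.

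Much of that stands. A reader might infer that the plan prescribes ten separate, uncorrected tests of its main hypothesis. The documents do not support this:
- Separate testing by day and specimen is an inference from the method named, not a statement.
- Ten is a ceiling, and the schedule supports eight.
- The lack of a correction shows only that the article is silent.
- The Abstract states the main hypothesis in terms of severity and mortality, the primary outcome is clinical improvement, and no success rule rests on viral load. One virological result, the day-14 removal rate, is singled out.

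It is also fair to object that averaging over days is a choice, not a correction. A drug started at day 0 need not show its full effect by day 3, and the table above shows the average losing to a single affected day at ρ = 0.5 once one day of four is unaffected.

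What the reply does not remove is that the article does state a method. That method is cross-sectional, one of its two options cannot use repeated measurements at all, and it is paired with an explicit plan to fill gaps with a mean or median.

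**Conclusion.** The point holds in a limited form. The only method the article states for continuous outcomes does not suit serial log10 viral load, and together with mean or median replacement it gives a less precise result resting partly on filled-in values.

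The size rests on assumptions. An average over five days has 0.44 to 0.84 of the one-day variance for ρ from 0.3 to 0.8, provided the effect is present throughout. Baseline adjustment brings the variance to 0.65 to 0.90 of that of a raw change, whether or not the effect persists. The false-positive figures apply only if the tests are run separately and each is read alone, which the article does not say. This is a worthwhile improvement to a secondary analysis. The primary conclusion is unaffected.

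**What to change.** In Statistical methods {20a}, add a rule for viral load:

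- Analyse log10 viral load with a linear mixed model for repeated measures, with baseline log10 viral load from the screening sample, arm, day and arm-by-day, and the patient as the repeated unit. Fit it to the observed data, and exempt this outcome from the mean or median replacement in {20c}.
- Name one specimen and one contrast in advance as the key viral-load comparison. Day 14 would match the virus removal rate. The average over the scheduled days is the alternative. One model per specimen without this choice would still leave two tests.
- Report the other days and the other specimen as estimates with confidence intervals.
- Reconcile day 21, which is in the endpoint list but has no RT-PCR in the schedule table.

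The cost is wording and some programming, with no new patients. The model needs an assumption for values below the detection limit, and it treats missing samples as explained by the observed data. An averaged contrast loses power if the effect is absent on one or more days. A day-14 contrast avoids that, but its gain then comes mainly from baseline adjustment and from using the earlier samples of patients with no day-14 value. The choice should be fixed before outcome data by arm are examined.
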